**Fig. 1 Fig1:**
[figure not shown]
Study trial profile and randomisation

### Blinding

The study is a pragmatic trial where blinding is neither possible nor desirable. However, outcome assessors and data analysts will be blinded to group allocation.

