### Randomisation

Each PCRU will continue to include subjects until the required total number of subjects (*n* = 600) is achieved (Fig. 1). All patients who give informed consent and who fulfil the eligibility criteria will be randomised. Participants are randomised to one of four treatments: ‘information and advice’; ‘physiotherapy, and information and advice’; ‘chiropractic care, and information and advice’; or ‘chiropractic care, physiotherapy, and information and advice’. A computer-generated, block randomisation list is produced to allocate participants to the treatment wings. The randomisation list and the allocation sequence are generated by a statistician who is not involved in the study. The sequence is concealed from the researchers involved in enrolling and assessing participants by using sequentially numbered, opaque, sealed envelopes. All researchers involved in the study will be blinded to block size(s) and randomisation list. Thus, the researchers do not know the block size(s) or if there is only one block size or different block sizes. This information (about block size(s) and randomisation list) is only known by the independent statistician who is not involved in the trial. The randomisation list will be in the possession of the statistician for the duration of the study. Envelopes will only be opened when it is time to allocate the intervention. The primary health care staff member opens the envelope during the phone call (but does not reveal the allocation to the participant), and schedules a time for the first visit. During the first visit at the PCRU, the health care provider (chiropractor and/or physiotherapist) will reveal which treatment group the participant has been randomised to.

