### Outcome measurements

A computer-based, self-reported patient questionnaire is used to collect data on back pain-related functional limitation, pain intensity, general health, HRQoL, and working status. Back pain-related functional limitation is measured by using the Oswestry Disability Index (ODI), pain intensity by using the Numeric Rating Scale (NRS), general health by using the general self-rated health (SRH) question and HRQoL is measured by the EuroQol 5 Dimensions 3 Levels (EQ-5D-3L) instrument [30–33].

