#### Primary outcome measure

##### Oswestry Disability Index (ODI) − A measure of back pain-related functional limitation

The ODI is a condition-specific instrument that measures back pain-related functional limitation [30]. It consists of ten questions where each question has six response choices and the value of each question ranges from 0 (no problems) to 5 (worst imaginable problems). A total ODI score is computed as the sum of scores on each question, and the total score of ODI varies between 0 (no problems) and 50 (worst imaginable problems). The total ODI score is then normalised to 0–100, by multiplying the (unadjusted) total score by 2. The ODI normalised score, based on the ODI outcome measure at 6 months, is our primary outcome measure [12]. The ODI has a high reliability, validity, and responsiveness, and is easy to administrate and is sensible to find clinical changes in treatment of patients with CLBP [34, 35].

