#### Secondary outcome measures

##### Numeric Rating Scale (NRS) – A measure of pain intensity

The NRS is an 11-grade scale ranging from 0 (no pain) to 10 (worst pain imaginable). The NRS is often used in clinical trials and by clinicians to measure self-reported pain intensity. It is easy to administrate and has a high responsiveness [31]. Each participant is asked to state their currently experienced pain using the NRS.

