### Data collection

Data will be collected at baseline (after randomisation and before the treatment starts), and at follow-up, 3, 6, and 12 months after baseline. Each participant fills out a computer-based questionnaire at each measurement occasion. The day before each follow-up occasion, each participant is sent a reminder by email to fill out the questionnaire. If needed, a second and a third reminder is sent 2 and 7 days after the follow-up occasion. All data will be obtained from the computer-based questionnaire and from the chiropractor and/or physiotherapist reporting the number and content of treatments.

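### The Blinding section promises blinded outcome assessors, but every effectiveness outcome is self-reported by participants who know their allocation

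*Protocol article*

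**What the plan says.** The Blinding section has two sentences. The first is general: "The study is a pragmatic trial where blinding is neither possible nor desirable". The second makes an exception: "outcome assessors and data analysts will be blinded to group allocation".

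Other sections describe how outcomes arise and who knows the allocation:

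- **Outcome measurements:** "A computer-based, self-reported patient questionnaire is used to collect data on back pain-related functional limitation, pain intensity, general health, HRQoL, and working status".
- **Primary outcome measure:** "The ODI normalised score, based on the ODI outcome measure at 6 months, is our primary outcome measure".
- **Secondary outcome measures, on pain:** "Each participant is asked to state their currently experienced pain using the NRS". Working status is likewise defined from self-report.
- **Data collection:** the participant completes the questionnaire on every occasion. The only other data source is reporting "from the chiropractor and/or physiotherapist reporting the number and content of treatments".
- **Randomisation:** at the first visit the health care provider "will reveal which treatment group the participant has been randomised to".
- **Discussion:** the difficulty of blinding patients is listed as a limitation. Expectation bias may work in either direction, and it cannot be estimated because no questions on expectations are asked.

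**The concern.** Blinded outcome assessment protects a comparison only if the person who produces the score does not know the arm. For a self-reported score that person is the participant. Here the participant knows the arm, so the Blinding section claims a protection that the design does not have.

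What is at stake is how the results are described and judged. If the sentence passes unchanged into the trial report, a reader who looks up blinding finds assessor blinding stated without qualification, and may rate the risk of bias in outcome measurement too favourably. The outcomes are subjective ratings of function, pain and health, together with self-reported working status. The arms differ visibly in what participants receive: information and advice alone, or the same with physiotherapy, chiropractic care or both. The QALYs are also built on the self-reported EQ-5D-3L, and resource use is recalled by the participant, so the exposure extends to the exploratory cost-effectiveness results.

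**Working it through.** No arithmetic beyond a count applies. The check sets the source of each effectiveness outcome beside what that source knows about allocation.

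**Step 1. Who produces each score?** From Outcome measurements, the sections on each instrument, and Data collection:

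| Outcome | Role | Produced by | Knows the arm at 3, 6 and 12 months? |
|---|---|---|---|
| ODI (6 months) | Primary | Participant | Yes |
| NRS | Secondary | Participant | Yes |
| Self-rated health | Secondary | Participant | Yes |
| EQ-5D-3L | Secondary | Participant | Yes |
| Working status | Secondary | Participant | Yes |

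Outcomes assessed by an unblinded person: 5 of 5. Outcomes assessed by a blinded person: 0 of 5.

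**Step 2. When does the participant learn the arm?** The Randomisation section has the envelope opened during the phone call without telling the participant, and the group disclosed at the first visit. Every follow-up score comes later. The Baseline section allows the questionnaire to be filled in 1 to 4 days before that visit, so some baseline scores may precede disclosure. That does not help the follow-up scores.

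**Step 3. Is there anyone else who could be the outcome assessor?** Data collection says that all data come from two sources: the participant's questionnaire and the treating chiropractor or physiotherapist. The clinician reports the number and content of treatments, which is not an effectiveness outcome, and necessarily knows the arm. The Randomisation section mentions researchers who enrol and assess participants, but under Data collection they produce no outcome data.

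**Step 4. Is the statement corrected elsewhere?** The Discussion says that patients are difficult to blind and that expectation bias is possible. It does not mention blinded outcome assessors, so it neither withdraws nor qualifies the Blinding statement.

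The conflict therefore lies between Blinding on one side and Outcome measurements, Data collection and Randomisation on the other.

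**The case against.** The strongest reply is that the risk is already in the open. The sentence just before the disputed one says that blinding is not possible, and the Discussion names unblinded patients and expectation bias as limitations. It does not list blinded outcome assessment among the strengths; the strength it claims is that researchers are blinded to allocation in the randomisation process. Open self-report is common in pragmatic trials and is not an error in itself. This stands, and it limits the point to one inaccurate statement rather than a concealed bias or a faulty design.

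A second reply is that outcome assessors may loosely mean staff who handle or score questionnaires. The article never says so, and blinding such staff would not protect against biased self-report. This reply would change the fault from a wrong statement to an undefined term, but the sentence would still need rewording.

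A reader might also draw stronger conclusions that the document does not support:

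- **That the Discussion contradicts the Blinding section.** It does not. One speaks of patients, the other of assessors and analysts.
- **That analyst blinding is untrue as well.** Treatment counts and content could reveal the arm to anyone who sees them, but nothing says that they are in the primary analysis dataset. The primary analysis uses ODI change by group, and the adjusted model lists only baseline characteristics. How datasets and arm codes are kept apart is commonly left to a fuller document.
- **That the primary contrast is hands-on care against a booklet.** The planned test is a four-group ANOVA with post hoc pairwise comparisons. Physiotherapy is described mainly as training and exercise, and the control group also has an initial examination and oral advice.
- **That comparisons among the three active arms are less exposed to expectation bias.** Expectations are not measured and the bias may run either way, so the document gives no basis for ranking the contrasts.

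**Conclusion.** The concern holds for the assessor half of the sentence. The trial does not have blinded outcome assessment for any of its five effectiveness outcomes, including the primary one, so the Blinding section is wrong as written. The analyst half is not contradicted and can stand; it guards against choices made in analysis, not against how participants answer.

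The conclusion rests on two readings: that the assessor of a self-reported score is the person who reports it, and that the two data sources named under Data collection are the complete list, as the section says. The direction and size of any bias in the treatment differences are unknown, and the trial's own data cannot estimate them. No test, sample size or data collection procedure is affected. What changes is the accuracy of the blinding claim and how between-group differences should be read.

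**What to change.** Replace the second sentence of the Blinding section with wording such as:

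> Participants and treating clinicians are not blinded. All effectiveness outcomes are self-reported, so outcome assessment is not blinded. Data analysts work with coded arms.

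Carry the Discussion's caveat on expectation bias into the interpretation of between-group differences in the report.

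An optional, inexpensive safeguard for analyst blinding is to keep the clinician-reported number and content of treatments out of the effectiveness dataset until the primary analysis is locked.

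The cost is a change of wording and, if the safeguard is adopted, a simple separation of data files. The stated blinding becomes less favourable, but it then matches the design.

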### Study treatments

During the first (baseline) visit all participants will meet a chiropractor and/or a physiotherapist for an initial examination which includes diagnosis and the medical history of the patient. The participants are randomised to one of four treatment groups:
*Information and advice*: participants are given oral and written information on how to manage non-specific CLBP and advice about the importance of staying active and avoiding rest. Each participant is given a booklet with information on how to stay active [7, 29]
*Physiotherapy, and information and advice*: the treatment primarily involves training and exercise such as stabilisation training, functional training, mobility training and postural control [7]. The duration, number and content of the treatment is at the discretion of the physiotherapist. Participants are also given information, advice, and a booklet [29]
*Chiropractic care and information and advice*: the treatment primarily involves spinal manipulation defined as a high-velocity, low-amplitude movement at the limit of joint range that takes the joint beyond the passive range of movement [7]. The duration, number, and content of the treatment is at the discretion of the chiropractor. Participants are also given information, advice, and a booklet [29]
*Chiropractic care, physiotherapy, and information, and advice*: the treatment primarily involves a combination of spinal manipulation (defined as a high-velocity, low-amplitude movement at the limit of joint range that takes the joint beyond the passive range of movement) and training and exercise (e.g. stabilisation training, functional training, mobility training and postural control) [7]. The duration, number, and content of the treatment is at the discretion of the chiropractor and physiotherapist. Participants are also given information, advice, and a booklet [29]

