### Setting

The study will be conducted at six primary care rehabilitation units (PCRUs) in Stockholm County Council, Sweden. If needed, additional units will be included. The operations manager for each PCRU has signed a written certificate to assure that they will provide sufficient resources to both carry out the study and guarantee the safety of the participants. The PCRUs are reimbursed through the Stockholm County Council. Twelve PCRUs in the Stockholm County Council were initially informed about the study by email and invited to participate. For each of the six PCRUs interested in participating, an information meeting was scheduled. Before the start of the study each PCRU was informed about the study methods in more detail and given the opportunity to give feedback on how to improve the efficiency in the recruitment of participants.

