#### Required sample size

A change of 10 percentage points on the ODI scale is usually defined as the minimal clinically important difference (MCID) [45]. To detect a reduction of 10 percentage points (SD of 15) in the ODI score, which is in agreement with the study of Davidson et al. [45] and Hägg et al. [46], with a two-sided 5% significance level and a power of 80%, a sample size of 150 patients per group will be necessary, given an anticipated dropout rate of 20%. Each PCRU will recruit subjects until the required number is achieved. The enrolment period will extend over 33 months. The projected sample size will provide sufficient statistical power for linear mixed regression and Generalised Estimating Equation (GEE) models considering compound symmetry of the covariance structure and the number of repeated measures [47]. Further, a change of 10–30 percentage points in the NRS scale is usually defined as a MCID [48, 49]. To detect a reduction of 10 percentage points in the NRS, with a two-sided 5% significance level and a power of 80%, a sample size of 146 patients per group will be necessary, given an anticipated dropout rate of 20%.

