#### Primary outcome measure

The primary analysis is to evaluate between-group differences in percentage point change in ODI scores at 6 months compared to baseline. One-way analysis of variance (ANOVA) will be used to evaluate the between-group difference for the primary outcome variable ODI at 6 months. A Levine’s test will be employed to check the assumption of equality of variance for the ANOVA. Assumption of normality will be checked by using skewness and normal probability plot. In case of violation of the normality assumption, we will use the non-parametric Kruskal-Wallis H test which does not require the assumption of normality. If the assumption of homogeneity of variance is violated we will use, the Welch or the Brown and Forsythe test. If the overall ANOVA is significant, we will perform further analysis using a Tukey or Games-Howell post hoc pairwise comparison. We will use Games-Howell if there is a violation of the equality of variance assumption. To evaluate effect size, we will present the difference between means, 95% confidence interval and the partial eta-squared (*η*
^2^).

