#### Additional analysis for percentage point change in ODI

Two additional analyses will be carried out for the primary outcome variable ODI at 6 months. First, an adjusted analysis will be used to control for baseline variables (age, sex, education, smoking status, physical activity, use of pain killers). This multiple linear regression analysis will adjust for potential predictor variables which might reasonably be expected to be predictive of favourable outcomes. We will perform residual analysis to assess model assumptions and goodness-of-fit. Secondly, a subgroup analysis will be performed to detect differences between groups of patients with an ODI normalised score at baseline either less than 40% or equal to or greater than 40% [12].

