#### Secondary outcome measures

Additional analysis of ODI will be done to evaluate the percentage point change in ODI scores and improvement at 3 and 12 months, respectively. Since the trial involves repeated measures data, a linear mixed model will also be used to analyse the secondary outcome measure. To account for repeated measures, to model within-subject variance, and to handle correlated data of continuous variables we will use a linear mixed model. An interaction term will be introduced in the model to examine heterogeneity effect.

The effect of treatment will be evaluated separately for each outcome variable (both primary and secondary) by using a linear mixed model. For binary and ordinal outcome variables a GEE will be employed. The latter model will be used to evaluate the effect of treatment on physical activity at 3, 6, and 12 months.

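### No planned model includes unit or clinician: omitting unit costs precision, and omitting clinician understates between-arm standard errors if outcomes vary by clinician

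*Protocol article*

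**What the plan says.** **Delivery.** On the physiotherapy arm, Study treatments states: "The duration, number and content of the treatment is at the discretion of the physiotherapist". It says the same of the chiropractor in the chiropractic arm and of both clinicians in the combined arm. The advice arm has no such clause. The Design section adds that Sweden has no official guideline on content or number of sessions. The Setting section states: "The study will be conducted at six primary care rehabilitation units (PCRUs) in Stockholm County Council, Sweden", and allows further units if needed.

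**Analysis.** For the primary outcome: "One-way analysis of variance (ANOVA) will be used to evaluate the between-group difference for the primary outcome variable ODI at 6 months". The fallbacks are Kruskal-Wallis, Welch or Brown-Forsythe, with Tukey or Games-Howell comparisons after a significant overall test. In the additional analysis, "an adjusted analysis will be used to control for baseline variables (age, sex, education, smoking status, physical activity, use of pain killers"; the list holds patient characteristics only. Under Secondary outcome measures: "To account for repeated measures, to model within-subject variance, and to handle correlated data of continuous variables we will use a linear mixed model".

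**Design calculation.** The only correlation mentioned under Required sample size is that between repeated measures on the same patient.

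**What is not given.** The article states neither the number of treating clinicians nor an ICC. Recruitment procedures mentions one chiropractor and one physiotherapist per unit, but as enrolment coordinators.

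**The concern.** All the named methods treat different patients as independent. If some clinicians get better outcomes than others, patients of the same clinician are correlated. Individual randomisation does not cancel this in the physiotherapy versus chiropractic comparison, because the clinicians belong to different professions and are nested in the arms. Variation between clinicians is then averaged as if it came from about 120 independent patients per arm. Confidence intervals are too narrow and the error rate exceeds 5%.

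Such variation is plausible here. The national survey described in the Background shows mixed practice among physiotherapists: 69% often used circulation training and 13% regularly used spinal manipulation. That survey concerned acute pain, though the article considers that it probably reflects chronic pain too. The trial is meant to inform guidelines, so its conclusions should reach beyond the clinicians who took part.

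PCRU is a separate matter. Every unit can contribute patients to every arm, so a common unit effect is shared across arms. What is at stake there is precision.

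**Working it through.** **1. The plan's own figure.** Required sample size states "To detect a reduction of 10 percentage points (SD of 15) in the ODI score", and "with a two-sided 5% significance level and a power of 80%, a sample size of 150 patients per group will be necessary", allowing for 20% dropout.
- n = 2 × (1.96 + 0.84)² × 15² / 10² = 35.3, so 36 evaluable per group, and 36 / 0.8 = 45 randomised.
- The stated 150 is not reproduced. That is a separate matter. Here 150 serves only to give 150 × 0.8 = 120 evaluable per arm.

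**2. Omitting PCRU.** The planned ANOVA was simulated with no treatment effect (480 evaluable patients, six units, 4,000 runs per scenario, simulation standard error about 0.3 percentage points at 5%). Unit ICCs are assumed.
- No clustering: 5.1% rejections.
- Common unit effect, allocation not balanced by unit: 5.3% at unit ICC 0.05 and 5.0% at 0.10.
- Common unit effect, allocation balanced within units: 4.4% and 3.9%.

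The error rate is therefore about nominal or conservative. Removing unit variance multiplies the standard error by about √(1 − ICC): √0.95 = 0.975 and √0.90 = 0.949, a gain of about 2.5% to 5%.

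**3. Omitting clinician.** Assumptions: k = 6, 12 or 18 clinicians per profession (one to three per unit), ICC 0.01 to 0.05, no clustering in the advice arm, and different clinicians in the two single-therapy arms.
- Patients per clinician per arm: m = 120 / k.
- Design effect: DE = 1 + (m − 1) × ICC.
- True over naive standard error: √((DE + 1)/2) for active versus advice, √DE for physiotherapy versus chiropractic care.
- True error rate of an unadjusted pairwise test: 2 × [1 − Φ(1.96 / ratio)].

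| k (m) | ICC | DE | Ratio, active v advice | Error rate | Ratio, physio v chiro | Error rate |
|---|---|---|---|---|---|---|
| 6 (20) | 0.01 | 1.19 | 1.05 | 6.1% | 1.09 | 7.2% |
| 6 (20) | 0.02 | 1.38 | 1.09 | 7.2% | 1.17 | 9.5% |
| 6 (20) | 0.05 | 1.95 | 1.21 | 10.7% | 1.40 | 16.0% |
| 12 (10) | 0.01 | 1.09 | 1.02 | 5.5% | 1.04 | 6.0% |
| 12 (10) | 0.05 | 1.45 | 1.11 | 7.7% | 1.20 | 10.4% |
| 18 (6.67) | 0.01 | 1.06 | 1.01 | 5.3% | 1.03 | 5.7% |
| 18 (6.67) | 0.05 | 1.28 | 1.07 | 6.7% | 1.13 | 8.4% |

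A ratio of 1.17 means that the naive standard error is 1 − 1/1.17 = 15% too small.

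**4. The planned overall test with shared clinicians.** The same simulation was run with one physiotherapist and one chiropractor per unit, both also treating the combined arm.
- Overall F test: 9.1% at ICC 0.02 and 15.3% at 0.05.
- Unadjusted pairwise tests at ICC 0.05: about 11% for any active arm versus advice, 16% for physiotherapy versus chiropractic care, and 7% to 8% for a single therapy versus the combination.

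**5. Power.** At 120 per arm, power for 10 points is 99.9% without clustering, 95.9% at DE 1.95, and 86% at DE 2.90 (ICC 0.10 with six clinicians).

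**The case against.** The strongest reply has four parts.

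- **Inferential target.** Clinician discretion is deliberate in a pragmatic trial, and one may regard these clinicians as the setting studied rather than as a sample. This is a legitimate choice, but it sits uneasily with the stated aim of informing guidelines. It supports treating the clinician model as a sensitivity analysis rather than the primary analysis.
- **Shared dose is not shown.** Discretion is exercised patient by patient, so patients of one clinician need not receive similar treatment. This stands: discretion makes clinician effects plausible, not certain.
- **The size is assumed.** With 18 clinicians and an ICC of 0.01 the inflation is negligible. All participants meet a chiropractor and/or a physiotherapist at the first visit, so the advice arm may share clinician effects that partly cancel. The pairwise rates in the table ignore the Tukey or Games-Howell step. All of this stands, although the simulated overall test is inflated too under the same kind of assumption.
- **The SAP may cover it.** A sensitivity analysis could be specified there. But the article itself fixes the primary model as one-way on treatment group and lists the covariates of the adjusted model. Neither contains unit or clinician.

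A reader might also infer that leaving out PCRU makes standard errors too small, or that only a few clinicians treat in each arm. The documents support neither. Randomisation is by patient, so a common unit effect does not shrink the standard error; only treatment effects that differ between units would. The number of treating clinicians is not stated, and units may be added.

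**Conclusion.** The point holds in a limited form. No planned model contains PCRU or clinician. Leaving out PCRU loses a little precision, or makes the test conservative if allocation is balanced within units. Leaving out clinician understates between-arm standard errors if outcomes vary by clinician.

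With 120 evaluable patients per arm, 6 to 18 clinicians per profession and an ICC of 0.01 to 0.05, an unadjusted 5% test runs at about 5.3% to 11% for active versus advice and about 5.7% to 16% for physiotherapy versus chiropractic care. Single-therapy comparisons with the combined arm are less affected if clinicians are shared. The clinician numbers and ICCs are assumptions, so the documents do not show that the inflation is present or large.

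Nor do they support reading this as a loss of power for the 10-point difference: 120 per arm tolerates a design effect of 120 / 36 = 3.3. The exposure is in error rate and interval coverage. It matters because, with SD 15 and no clustering, 120 per arm has 80% power for a difference of only 5.4 points, so effects well below 10 points can reach significance.

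**What to change.** 1. Add PCRU as a fixed factor to the primary ODI model and the secondary models, for precision. The one-way fallbacks then need restating for a model with two factors.
2. Record a coded identifier for every treating clinician on the existing treatment report, with two in the combined arm.
3. Pre-specify a sensitivity analysis of the primary outcome with separate random effects for physiotherapist and chiropractor. It should allow the same clinician to appear in more than one arm and use a small-sample degrees-of-freedom correction. A simple partially nested model would not fit, because combined-arm patients have two clinicians.

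**Cost.** Five degrees of freedom for six units, one or two coded fields, some wording, and possibly wider intervals in the sensitivity analysis. No extra patients and no change to treatment. The identifiers should be collected while the trial runs, since they may not be recoverable later.
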